### Definition of populations included in the analysis

The analysis of the primary endpoint will be performed on the mITT population comprising all randomized patients with glioblastoma IDHwt. Subjects will be analysed in the study arms to which they were randomized, irrespective of protocol violations.

The ITT population of all randomized patients (incl. the patients with IDHmut diffuse high-grade glioma) will be used for sensitivity analyses of survival, QoL-endpoints, mRS and safety analyses. The ITT population is identical to the safety population.

If subjects undergo surgical treatment with an intervention different from the one assigned according to the randomization schedule, safety analyses will be conducted based on the intervention actually received ("as treated" analysis) rather than the assigned randomization group.

The PP population is a subset of the mITT population and is defined as the group of patients with a glioblastoma IDHwt who had no major protocol violations, and underwent the examinations required for the assessment of the endpoints at predefined times. The PP population will be used for sensitivity analyses.

Additionally, a separate exploratory analysis of OS, PFS, and QoL endpoints will be conducted for the subgroup of patients with IDH-mutant diffuse high-grade glioma, expected to comprise approximately 4.5% of the study population.

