### Endpoints

The primary endpoint is OS in the modified intention-to-treat (mITT) population, defined as all randomized patients with histologically confirmed glioblastoma (CNS world health organization (WHO) grade 4, isocitrate dehydrogenase (IDH)-wildtype (wt)). If significant differences in OS are observed, the patient-reported QoL domain "global health status" from the European organization for research and treatment of cancer (EORTC) QLQ-C30 questionnaire will serve as a co-primary endpoint. Overall superiority of ATL requires a significant improvement in OS alongside non-inferiority in the development of global health status over time within the mITT population. Secondary endpoints include OS in the population of all patients randomized in the trial (intention-to-treat, ITT population) and in the per-protocol (PP) population. The QoL domain "global health status" from the EORTC QLQ-C30 questionnaire will also serve as a co-endpoint in these analyses, analogous to the primary endpoint. PFS, measured from the day of randomization until diagnosis of progressive disease based on MRI (RANO 2.0 criteria) [27], will be analyzed in the ITT, mITT, and PP populations. Separate OS and PFS analyses will also be conducted for patients with IDH-mutant gliomas. Further secondary endpoints will be evaluated in the mITT population and include QoL across six preferred domains of the EORTC QLQ-C30 and BN20 questionnaires (global health status, physical functioning, social functioning, cognitive functioning, communication deficit, and motor dysfunction), as well as all other domains of these questionnaires. Additional endpoints include PFS (as defined above), the KPS, the mRS, neurocognitive functioning assessed using the Verbaler Lern- und Merkfähigkeitstest (VLMT) [28, 29], the Boston Naming Test [30], and EpiTrack® [31], as well as seizure outcomes classified according to the International League Against Epilepsy (ILAE) [32].

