^b^ for women with childbearing potential

^c^ after day 90 visit (first 12 week FU): every 24 weeks

^d^ only until day 90

Postoperative visits are scheduled as follows: Visit 4 will occur on Day 1 (early postoperative), Visit 5 on Day 3 (postoperative), Visit 6 on Day 14, Visit 7 on Day 30, and Visit 8 on Day 90. Subsequent follow-up visits will be conducted every 12 weeks (± 5 days) until death. AEs will be assessed according to CTCAE5, starting from Visit 2 and continuing through Visit 7. Particular attention will be given to postoperative complications, which will be recorded from Visit 4 through Visit 8, with potential late-onset complications assessed during Visit 8.

Timing deviations from the defined schedule are considered protocol violations under certain conditions. For Visit 6, a deviation of more than 2 days is regarded as a violation, while for Visit 7 and all subsequent visits, deviations of more than 5 days are considered violations. No deviations are permitted for Visits 2 through 5.

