#### MRI protocols

All MRI examinations have to include the following sequences:Pre-contrast injection: T2-w (e.g., turbo-spin-echo, TSE); T2-FLAIR; 3D T1-w (e.g., gradient-echo, GRE; or T1-w in two planes, one of them axial)Post-contrast injection: 3D T1-w (e.g., gradient-echo GRE; or T1-w in two planes, one of them axial)

Additional sequences are optional but can be included at the discretion of the treating physician.

For T2, FLAIR, DWI, and SWI/T2* sequences that are not performed in 3D, it is recommended to acquire the images in the axial plane to ensure structured and comparable evaluation. To ensure the reproducibility of MRI evaluation, all MRIs have to be reviewed post-hoc by the reference neuroradiologist [name]. [name] (Department of Neuroradiology, University Hospital Bonn). The MRIs will be sent blinded regarding the participating center (only labelled with the Randomization-ID) to the reference neuroradiologist to ensure an unbiased progression assessment.

Mandatory MRI examinations will be conducted as part of the standard treatment protocol. These include a preoperative MRI (baseline visit; any MRI performed within one week prior to surgery can be considered as the baseline MRI), an early postoperative MRI (performed within 72 h after surgery), and follow-up MRIs every three months after surgery. Additionally, a post-radiation MRI within four weeks of completing radiotherapy is recommended but not mandatory.

To evaluate protocol adherence regarding the surgical procedures in the experimental (ATL) and control (GTR) arms, the 72-h postoperative MRI will be reviewed by two experienced neurosurgeons. The resection results will be graded as follows:GTR: Resection cavity without remaining contrast-enhancing tissue, subtotal resection, or partial resection.ATL: Anatomical boundaries for ATL (as described above) fulfilled or not fulfilled.

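### Read literally, the per-protocol set can lose a patient at every late or missed follow-up visit, so its OS and PFS results are selected on survival time

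*Protocol article*

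**What the plan says.** Under Definition of populations included in the analysis, the PP set is the part of the mITT population that is free of major violations and that also "underwent the examinations required for the assessment of the endpoints at predefined times". The two conditions are joined by a plain conjunction. The timing condition is therefore additional to the one on major violations, and it carries no limit on the number of visits and no tolerance.

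The predefined times are in Time schedule of measurements, in the text after Table 1. Visits fall on days 14, 30 and 90, and then: "Subsequent follow-up visits will be conducted every 12 weeks (± 5 days) until death". The same text adds that "for Visit 7 and all subsequent visits, deviations of more than 5 days are considered violations". The section Protocol violations also counts missed and mistimed evaluations as violations.

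On the use of the set, the populations section says "The PP population will be used for sensitivity analyses". Endpoints goes further: it lists OS "and in the per-protocol (PP) population" as a secondary endpoint and says that PFS "will be analyzed in the ITT, mITT, and PP populations". Primary outcome repeats the OS and QoL analyses in the PP set and undertakes to discuss relevant differences between the mITT, ITT and PP results.

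**The concern.** A patient who dies at five months has few scheduled visits at which to fail the timing condition. A patient who lives four years has many. With any non-zero rate of late or missed visits, the chance of staying in the PP set falls with survival time, so the set is chosen partly by the outcome it is used to estimate.

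Three things follow. PP survival curves are too short in both arms. If ATL prolongs survival, ATL patients accrue more visits and are removed more often, which pulls the HR towards 1 when adherence is equal by arm. And a gap between the PP and mITT results, which the protocol promises to discuss, could come from the set definition alone.

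The timing condition also gives the OS analysis nothing. OS is defined as time from randomization to death and needs only survival status.

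**Working it through.** **Inputs from the protocol article.** Sample size calculation: median OS 17 (GTR) and 27.5 months (ATL), two-sided 5% log-rank test, 36 months of accrual plus 36 months of follow-up, 170 evaluable patients, 80% power. Time schedule of measurements: days 14, 30 and 90, then every 84 days. Days 1 and 3 are left out of the count.

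**Assumption.** The documents give no rate of late or missed visits. Let p be that rate per visit, independent between visits and equal in both arms, shown at 2%, 5% and 10%.

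**Step 1: reproduce the plan's figure.**
- HR under exponential survival = 17/27.5 = 0.618.
- Schoenfeld events = 4(1.96 + 0.84)²/(ln 0.618)², which rounds up to 136.
- Event probability per arm = 1 − (e^(−36λ) − e^(−72λ))/(36λ), with λ = ln 2/median. This gives 0.879 (GTR) and 0.735 (ATL), mean 0.807.
- N = 136/0.807 = 168.5, so 169. At N = 170, 137.2 events are expected and power is 80.4%. The stated 170 reproduces, so these survival assumptions are a fair base.

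**Step 2: how retention depends on survival.** A patient with v scheduled visits stays in the PP set with probability (1 − p)^v. At p = 5%:
- death at 12 months: v = 3 + 3 = 6, retention 0.95^6 = 0.74;
- alive at 36 months: v = 3 + 11 = 14, retention 0.95^14 = 0.49.

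Under the design assumptions the mean number of visits up to death or censoring is 9.2 in GTR and 12.0 in ATL.

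**Step 3: effect on PP OS.** This was simulated with 400,000 patients: exponential survival, censoring uniform between 36 and 72 months, and patients kept with probability (1 − p)^v. Medians vary by about 0.1 month between runs.

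| Late or missed per visit | HR | Median GTR / ATL (months) |
|---|---|---|
| none (mITT) | 0.62 | 17 / 27.5 |
| 2% | 0.64 | 14.7 / 23.0 |
| 5% | 0.68 | 12.0 / 17.5 |
| 10% | 0.74 | 8.9 / 11.7 |

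At 5%, about 66% of GTR and 58% of ATL patients remain, or about 105 of 170. Retention is 85% among patients dying before 12 months and 38% among those living beyond 36 months. In trial-size runs (2,000 replications) the PP log-rank test has power of about 68%, 45% and 23% at 2%, 5% and 10%.

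**Step 4: no treatment effect.**
- Equal survival and equal adherence: the HR stays at 1.00, but the medians are still too short (at p = 5%, about 12 months instead of 17).
- Equal survival (median 17 months), with 98% of visits on time in one arm and 95% in the other: HR 1.20 if the GTR arm attends better, 0.84 if the ATL arm does. Both are spurious.

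PFS was not simulated. The same mechanism applies, because membership depends on visits accrued during follow-up.

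**The case against.** The strongest defence is an endpoint-specific reading. The clause concerns examinations needed to assess the endpoints, OS needs only survival status, and so a late visit would remove nobody from PP OS. The article also calls timing deviations violations only under certain conditions and never calls them major. Violations are to be listed and their impact discussed before the analysis, and tolerances may be set in an analysis plan that is not shown. This has some weight: the literal reading is not the only one. But the article defines a single PP set for OS, PFS and QoL, keeps the timing condition separate from the one on major violations, and sets no tolerance. An analysis plan that adopts this wording inherits the problem.

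It is also fair that the consequence is limited. OS and QoL are tested in the mITT population irrespective of violations, so no confirmatory conclusion rests on the PP set.

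Three stronger readings are tempting and should not be adopted.

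- **A larger bias.** Adding a constant exclusion hazard k = −ln(1 − p)/(84/30.44) per month to each arm's hazard gives HRs of 0.68, 0.74 and 0.80 at 2%, 5% and 10%. That ignores administrative censoring. Survivors censored between 36 and 72 months stop accruing visits and can stay in the set, so the shift is smaller.
- **A PP result that always understates ATL.** This holds only with a real benefit and equal adherence (step 4).
- **Crossed-over patients counted as adherent.** MRI protocols grades the arms on different scales: residual enhancement for GTR and, for the other arm, "ATL: Anatomical boundaries for ATL (as described above) fulfilled or not fulfilled". A reader might infer that a lobectomy-sized control resection passes as adherent. The text does not say so. No section makes this grading the PP rule, and the populations section recognises patients who receive the other intervention.

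**Conclusion.** The point holds for the PP definition as written. PP OS and PFS are selected on survival time. The direction for the survival curves is clear: too short in both arms. For the HR, the design assumptions with equal adherence give a move from 0.62 to about 0.64, 0.68 or 0.74 at 2%, 5% or 10% of visits late or missed. At 2% that is minor. At 5% the set also loses over a third of its patients and the medians are well below the true ones.

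These sizes rest on an adherence rate that the documents do not give, on independent visits, on exponential survival and on every mistimed visit leading to exclusion. They apply to OS only. The matter is confined to secondary and sensitivity analyses, so it is a definition worth correcting and not a threat to the primary result.

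**What to change.** For OS and PFS, remove follow-up visit timing and completeness from the PP definition. Define the set by facts settled early: confirmed IDH-wildtype glioblastoma, eligibility met, and the allocated resection performed as verified on the 72-hour MRI. If those criteria are unrelated to prognosis, the PP analysis then targets the same quantities as mITT (HR about 0.62, medians about 17 and 27.5 months). Whether the allocated resection was achieved may itself relate to prognosis, so the usual caution about PP analyses remains, but exclusion no longer accumulates with time alive.

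If a timing rule is wanted for the QoL analysis, state it for that endpoint alone.

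The cost is a wording change in the protocol and analysis plan, made before outcome data are seen. The MRIs and their review by two neurosurgeons are already planned, so no new data are needed.

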### Primary outcome

The statistical analysis will be conducted at the Study Center Bonn (SZB) of the University of Bonn Medical Center under the direction of [name]. [name]. The primary, confirmatory analysis will compare OS between the treatment groups using a two-sided log-rank test at a significance level of 5%. This analysis will be performed on the mITT population. The log-rank test will be stratified by age group (< 50 years or ≥ 50 years) and pre-operative KPS class (70–80% vs. 90–100%). Surviving patients and those lost to follow-up will be censored at the respective time points. OS will be summarized using Kaplan–Meier curves, with median survival estimates and corresponding 95% confidence intervals reported.

A sensitivity analysis for OS will be conducted using a Cox proportional hazards model with treatment group and MGMT promoter methylation status (hypermethylated vs. unmethylated) as independent variables. If the MGMT promoter methylation status is not available, missing data for these patients will be imputed. In another sensitivity analysis for OS, a Cox proportional hazards model with treatment group and center recruitment volume (high vs. low) will be fitted. Additionally, potential prognostic factors, including age, preoperative KPS, MGMT promoter methylation status (hypermethylated vs. unmethylated), and center recruitment volume (high vs. low), will be analyzed using a multivariate Cox proportional hazard model for OS.

If OS of ATL significantly differs from that of GTR, the patient-reported QoL domain "global health status" from the EORTC QLQ-C30 questionnaire will be analyzed as a co-primary endpoint. Changes from baseline in the experimental arm (ATL) will be compared to the standard arm (GTR) to assess non-inferiority, using a non-inferiority margin of 1.6 score points per year. This evaluation will be performed on the mITT population and using a linear mixed-effects model (QoL score as dependent variable, random patient intercept, treatment group + time as independent variables, estimating a 95% confidence interval of the interaction between time and treatment).

Overall superiority of ATL will require significantly prolonged OS alongside non-inferiority in the development of global health status over time. Due to the hierarchical testing approach, no adjustment of the type I error rate is necessary.

The above analyses will be repeated as a sensitivity analysis using the ITT population of all randomized patients, the PP population, and, exploratorily, the population of patients with IDHmut diffuse high-grade glioma. Any relevant differences between the results of the mITT, ITT and PP analyses will be critically discussed.

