#### Control intervention

Patients in the control arm will undergo GTR, defined as the removal of 100% of tumor tissue as visualized on gadolinium-enhanced MRI [9]. The extent of resection will be confirmed using early postoperative MRI (T2/FLAIR and gadolinium-enhanced T1 sequences) within 72 h after surgery.

In both treatment arms, resection will be followed by guideline-conform adjuvant first-line therapy. Options include:Standard radiochemotherapy with temozolomide (TMZ) according to Stupp et al. [37].For elderly patients (> 70 years), hypofractionated radiotherapy (RT) with or without TMZ chemotherapy, based on O-6-methylguanine-DNA methyltransferase (MGMT) promoter methylation status [38].For elderly patients, monotherapy with either RT or standard TMZ chemotherapy alone [39].For patients < 70 years with MGMT promoter-methylated glioblastoma, RT combined with CCNU/TMZ according to CeTeG/NOA-09 [40].Addition of tumor-treating fields (TTFs) is possible [41].

Participation in another interventional study is not permitted until progression, determined according to the response assessment in neuro-oncology (RANO) 2.0 criteria [27].

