
### Gender distribution

While some studies have suggested a potential prognostic role for gender in glioblastoma, with better survival observed in females compared to males [1, 42] recent analyses of large real-world data indicate that this difference disappears after adjusting for known prognostic parameters like the *MGMT* promoter methylation status as well as the chosen treatment modalities [43]. Moreover, according to major clinical guidelines, such as those from the National Comprehensive Cancer Network (NCCN) and the European Association for Neuro-Oncology (EANO) [44], gender is not considered a universally recognized prognostic factor in glioblastoma. Therefore, no specific gender ratio has been specified for this study.

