### Randomization

A unique feature of the ATLAS/NOA-29 trial is the intraoperative randomization process. Patients with imaging evidence suggestive of newly-diagnosed glioblastoma confined to the anterior temporal lobe will undergo craniotomy, typically performed as a pterional or temporal craniotomy, to allow for both temporal GTR and ATL. Once the dura is opened and tumor access is achieved, tumor tissue will be sent for frozen section analysis by the neuropathologist or pathologist in charge. Randomization will only occur after the (neuro)-pathologist has confirmed the diagnosis of diffuse high-grade glioma based on the frozen section results. The frozen section procedure, as performed in this study, is expected to prolong the surgery by approximately 10 to 20 min.

Randomization will be performed using the method of permuted blocks with variable block sizes. The randomization number will be assigned through the electronic case report form (eCRF) system, in a 1:1 ratio between the experimental (ATL) and control (GTR) interventions. Stratification will occur based on two criteria: age group (< 50 years or ≥ 50 years) and pre-operative KPS (70–80% vs. 90–100%).

Blinding of the surgical procedure is not feasible due to its inherent nature. The operating neurosurgeon and other treating physicians must review MRI scans during follow-up examinations, which will reveal the surgical approach. Consequently, the randomization process must be open.

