## Statistics and analysis

### Sample size calculation

The sample size calculation is based on the primary endpoints of OS and QoL, with equal allocation of subjects to the two treatment groups. Assuming a two-sided alpha level of 5%, median OS times of 17 months in the control group and 27.5 months in the experimental group, a 3-year accrual period, and a 3-year follow-up period (resulting in a total trial duration of 72 months), a total of 170 subjects with a confirmed diagnosis of glioblastoma will provide 80% power to test the null hypothesis of equal OS between the two groups (two-sided log-rank test). The assumed survival benefit of a 10-month improvement with ATL over GTR is based on existing data from retrospective glioblastoma surgery studies involving ATL [16, 25] as well as analyses of EORTC datasets that are not specific to temporal tumor localization [9].

It is anticipated that approximately 4.5% of randomized patients will not have glioblastoma CNS WHO grade 4 but rather a different subtype of diffuse high-grade glioma, as determined by the final integrated histopathological and molecular diagnosis according to the 2021 WHO classification [55]. If the final diagnosis does not confirm glioblastoma IDH wildtype (CNS WHO grade 4), these patients will remain in the trial for safety follow-up but will be replaced in their respective groups and excluded from the mITT population. This replacement strategy will result in a maximum of 178 randomized patients. All randomized patients, regardless of diagnosis, will undergo regular follow-up as outlined in the trial protocol for safety monitoring.

The two primary endpoints will be analyzed in a hierarchical order, with QoL being tested for non-inferiority in the experimental group compared to the control group if the null hypothesis for OS is rejected. QoL measurements will be conducted quarterly, and a prior study demonstrated an approximately linear time dependence of the QoL (= global health) score on time [49].

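### The confirmatory OS test is valid but can give up power, because MGMT status is left to non-confirmatory Cox models

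*Protocol article*

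**What the plan says.** The Primary outcome section compares OS in the mITT population with a two-sided 5% log-rank test. On its strata it says: "The log-rank test will be stratified by age group" (under 50 against 50 or over), together with KPS class (70–80% against 90–100%). The Randomization section uses the same two factors.

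MGMT is not ignored. The Primary outcome section plans a sensitivity Cox model "with treatment group and MGMT promoter methylation status (hypermethylated vs. unmethylated) as independent variables", with missing status imputed. It also plans a multivariable Cox model that names age, KPS, MGMT and centre volume. Neither carries the confirmatory decision.

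Elsewhere the article treats MGMT as important:
- Gender distribution says of a sex difference in survival that "this difference disappears after adjusting for known prognostic parameters", and MGMT status is the parameter it names next.
- Control intervention, which covers adjuvant therapy in both arms, has radiotherapy for older patients "with or without TMZ chemotherapy, based on O-6-methylguanine-DNA methyltransferase (MGMT) promoter methylation status". It also ties one combination regimen for patients under 70 to methylated tumours.
- Histopathological and molecular genetic results provides for MGMT to be determined and recorded, with a category for unavailable or inconclusive results.

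Randomization follows the intraoperative frozen section: "tumor tissue will be sent for frozen section analysis by the neuropathologist or pathologist in charge". Table 1 places histopathological results at the day 30 visit.

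**The concern.** Design cannot balance MGMT, because the result is not known when the patient is randomised. That leaves the analysis. If a strong prognostic factor is omitted from a survival comparison, the estimated treatment effect shrinks towards the null. Any chance imbalance between arms also passes into the confirmatory result. MGMT is a property of a tumour that is sampled before allocation, and the arm cannot alter it, so it is a legitimate covariate for the primary analysis.

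The trial has one confirmatory OS test, sized at 80% power with nothing to spare. The QoL non-inferiority test opens only if OS is significant. A missed OS result would therefore end confirmatory testing.

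**Working it through.** **1. The plan's own figure.** Inputs from Sample size calculation: "median OS times of 17 months in the control group and 27.5 months in the experimental group", 36 months of accrual, 36 months of further follow-up, 170 evaluable patients, 1:1 allocation, two-sided 5%. Exponential survival and uniform accrual are assumed.

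- Hazard ratio = 17/27.5 = 0.618; ln(0.618) = −0.481.
- Monthly hazards: ln 2/17 = 0.0408 (GTR) and ln 2/27.5 = 0.0252 (ATL).
- Event probability = 1 − [exp(−36λ) − exp(−72λ)]/(36λ) = 0.879 (GTR) and 0.735 (ATL); mean 0.807.
- Expected events = 170 × 0.807 = 137.2.
- Schoenfeld power = Φ(√137.2/2 × 0.481 − 1.96) = Φ(0.857) = 80.4%.

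The stated 80% reproduces. It presumes one common hazard within each arm, so no prognostic heterogeneity.

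**2. Assumptions needed for MGMT.** The article gives no prevalence and no hazard ratio. Assumed here: 40% methylated (30% and 50% as variants) and a hazard ratio for methylated against unmethylated between 0.35 and 1.0. The treatment hazard ratio is 0.618 within each MGMT class, and the control-arm mixture has a median of 17 months. With exponential survival in each class, the ATL curve is the GTR curve with time divided by 0.618. The ATL median is therefore 17/0.618 = 27.5 months, and both arm medians match the plan.

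The age-by-KPS cells were four non-prognostic strata with assumed shares of 5, 10, 35 and 50%. Each setting used 3,000 simulated trials of 170 patients with complete MGMT data. The Monte Carlo standard error of a gain is about 0.3 to 0.7 points.

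**3. Power at 40% methylated.**

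| MGMT HR | Planned (age, KPS strata) | Plus MGMT as covariate | Gain (points) | Gain if MGMT is an extra stratum |
|---|---|---|---|---|
| 0.35 | 64.2% | 76.8% | +12.6 | +11.3 |
| 0.40 | 68.0% | 77.5% | +9.5 | +7.4 |
| 0.50 | 72.4% | 78.0% | +5.6 | +3.6 |
| 0.60 | 74.8% | 77.9% | +3.1 | +1.6 |
| 0.70 | 76.5% | 77.6% | +1.1 | −1.3 |
| 0.80 | 77.4% | 77.5% | +0.1 | −1.7 |
| 1.00 | 78.6% | 78.6% | about 0 | −2.0 |

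The last row lies a little below 80.4% because the simulated test is split over four strata and carries Monte Carlo error (√(0.8 × 0.2/3000) = 0.7 points). The comparison that matters is between columns, not against 80%.

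At 30% methylated the covariate gains are +7.8, +5.4 and +2.7 points for hazard ratios 0.4, 0.5 and 0.6. At 50% methylated they are +10.4, +4.5 and +2.7.

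**4. Type I error.** With no treatment effect and an MGMT hazard ratio of 0.5: 4.7% for the planned test and 4.9% with the covariate.

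**5. Chance imbalance.** With 85 per arm, the standard deviation of the between-arm difference in methylated share is √(0.4 × 0.6 × 2/85) = 0.075. A difference above 10 points in either direction has probability 2 × [1 − Φ(0.10/0.075)], about 18%. At an MGMT hazard ratio of 0.5, the planned test's power is 54% when such an imbalance is against ATL and 87% when it favours ATL. With MGMT as a stratum the figures are 74% and 73%.

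**6. Agreement of verdicts.** The planned and covariate-adjusted tests differ on significance in about 7% (hazard ratio 0.6), 10% (0.5) and 14 to 15% (0.4) of trials.

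**The case against.** The strongest reply is that nothing here is an error. Stratifying the test by the randomisation factors is standard practice, the test matches the one used for sample size, and type I error is nominal either way. MGMT-adjusted Cox analyses are already specified, so the only question is which analysis carries the confirmatory label. All of this stands, and it makes the point one of efficiency rather than validity.

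Three stronger readings are tempting, and the documents support none of them.
- **That the plan loses a fixed number of points.** The size rests entirely on an MGMT effect the article does not state. At a hazard ratio of 0.8 or weaker there is practically no loss.
- **That chance imbalance decides the result.** Randomisation holds the overall error rate at 5%, and the two tests agree in about 85 to 93% of trials at hazard ratios of 0.4 to 0.6.
- **That the sample size is wrong.** It reproduces under its own assumption.

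Two practical objections also have weight. MGMT may be unavailable or inconclusive, and the table assumes complete data. A further simulation with 10% missing, handled as a separate category, still showed a gain at hazard ratios of 0.4 to 0.6. The article does not say that MGMT is assayed on the frozen-section sample, so the tumour property is fixed before randomisation but the availability of a result is not shown to be. And keeping the log-rank test as a sensitivity analysis leaves the same possible discordance with the labels exchanged.

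The planned sensitivity model does not remove the concern. It cannot change the confirmatory decision. As worded it contains treatment and MGMT but not age or KPS, so a discordant result could not be traced cleanly to MGMT.

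**Conclusion.** The point holds as a matter of efficiency and robustness. The confirmatory OS test leaves out a factor that the article calls prognostic and uses to guide adjuvant therapy, in a design where only the analysis can account for it. Moving MGMT into the confirmatory model costs nothing appreciable in power if MGMT is weakly prognostic. It gains about 3 points at a hazard ratio of 0.6, 5 to 6 at 0.5, 9 to 10 at 0.4 and up to about 13 at 0.35. These figures assume 40% methylated, exponential survival, a treatment hazard ratio of 0.618 within MGMT classes and complete MGMT data. A change is advisable; the plan as written would still give a valid test.

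**What to change.** Before database lock, and without sight of survival by arm, define the confirmatory OS test as the treatment term of a Cox model stratified by age group and KPS class, with MGMT as covariate. State in the same place how missing or inconclusive MGMT is handled: either the imputation already planned or a separate not-available category. Keep the present stratified log-rank test as a sensitivity analysis.

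Adding MGMT as a further log-rank stratum is not an equivalent solution. It gains less at every hazard ratio shown and loses 1 to 2 points at 0.7 or weaker.

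The change needs protocol and analysis-plan wording, but no new data or patients. It has two small costs: the hazard ratio becomes conditional on MGMT, and the handling of missing MGMT becomes part of the primary test.
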